### Statistical analysis

The primary outcomes of SILVER-AMI are the occurrence of all-cause hospital readmission, all-cause death, and decline in health status within six months of hospital discharge. Using independent risk factors that include cardio-centric factors (e.g. STEMI vs. NSTEMI, systolic blood pressure, Killip Class), as well as geriatric impairments, we will construct risk stratification models that predict the probability of each outcome for specific combinations of the risk factors. These models will be variants of the Cox regression models for the time-to-event outcomes (hospital readmission and mortality) and the logistic model used for decline in health status. Because mortality serves as a competing risk for hospital readmission, we will evaluate the associations of explanatory variables with both time-to-event outcomes using the competing risk approach of Fine and Gray [27]. All linearity assumptions will be checked graphically and deviations from model additivity will be accommodated by an examination of all statistically significant, clinically indicated two-factor interactions. All missing data will be examined for the nature of missingness, i.e., whether missing at random, and if justifiable, multiple imputation will be applied. Models will be evaluated with an examination of residuals and goodness-of-fit statistics using SAS/STAT ® V9.3 (SAS Institute, Cary, NC) or later, with statistical significance defined as a two-sided p-value <0.05.

Internal and external validation techniques will then be used to test the reproducibility of the risk stratification tools. For internal validation, jackknife methods [28] will be used to evaluate the percent of correct classification; external validation will be performed on the 500 randomly selected participants who were excluded from both model building and internal validation.

Once the final models have been developed, user-interface applications will be developed for “smart-phones” and other hand-held devices. The model coefficients for each outcome will be stored in hand-held applications whose outputs will provide the probability of each outcome. The inputs to the applications will consist of simple yes/no entries denoting the presence or absence of risk factors. Calculation will be presented in real time, and the results will list specific risk factors, and probability of the outcomes.

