Third, there are several specific products that will be developed from the data collected in SILVER-AMI. These include separate risk models for three outcomes (readmission, mortality, and decline in health status) that, once created, will be adapted for PC-based and smartphone use, similar to the Framingham Risk Calculator [36] or TIMI Risk Score [37]. Such decision aids may help to identify patients in need of resource intensive post-hospital interventions and therefore lead to improvements in real-time decision making at the point of care.

Finally, the recruitment network for SILVER-AMI includes approximately 70 sites across the U.S. in a variety of geographic settings. The network involves a large range of hospital sizes, as well as a mixture of academic and community hospitals, ensuring a diverse mixture of patients and practice patterns that will lend external validity to our findings. This network also has the potential to be used in future epidemiologic studies of other cardiac conditions, or for trials of interventions aimed at improving outcomes among older adults.

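### The applications will display probabilities, but the only validation measure named, percent correctly classified, does not test probabilities and can miss or reward miscalibration

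*Protocol article*

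**What the plan says.** All references are to the protocol article.

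- **Product.** In Statistical analysis, model coefficients are stored in hand-held applications "whose outputs will provide the probability of each outcome". The user enters the presence or absence of each risk factor. The Discussion places the tools at the point of care.
- **Model checking.** "Models will be evaluated with an examination of residuals and goodness-of-fit statistics". The statistics are not specified.
- **Validation.** This comes next: "Internal and external validation techniques will then be used to test the reproducibility of the risk stratification tools". For the internal part, "jackknife methods [28] will be used to evaluate the percent of correct classification", with no cut-off given. For the other part, "external validation will be performed on the 500 randomly selected participants who were excluded from both model building and internal validation", with no measure given.
- **Applications.** The paragraph after validation begins "Once the final models have been developed, user-interface applications will be developed". The Discussion says of the same models that they, "once created, will be adapted for PC-based and smartphone use".
- **Performance hypothesis.** The Background states it in terms of discrimination only.

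**The concern.** A clinician will read a number off the application: this patient's six-month risk of death, readmission or health status decline. For such a product the key property is calibration, that is, agreement between predicted and observed risk. Percent correctly classified first reduces each probability to a yes or no at some cut-off and then scores that call. It ignores how far a probability lies from the truth unless the error carries a patient across the cut-off.

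The listed goodness-of-fit statistics do not fill the gap. They belong to model evaluation, before validation. Fit in the data used for fitting does not reveal predictions that are too extreme for new patients.

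The applications also work from yes/no entries and stored coefficients, whereas the models may contain continuous factors such as systolic blood pressure. The displayed probability may therefore differ from the fitted one, which is a further reason to test the number as shown.

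At stake is whether displayed risks meant to identify patients for intensive post-hospital support could be materially wrong without the named check showing it.

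**Working it through.** **Inputs from the article (Sample size and power).** Development cohort 2500, validation cohort 500, mortality 28%, readmission 39%, health status decline 35% of survivors. The article's own validation figure reproduces: 500 × 0.28 = 140 deaths.

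**Assumptions, because the article gives neither.** The c-statistic and the cut-off. For mortality I use a normal distribution of true log-odds with SD 0.87 and mean risk 28%, which gives a c-statistic of about 0.72. The cut-off is 0.5 or the event rate, 0.28.

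**Formula.** Let p be the true risk and q the displayed risk, with logit q = logit p + d. Percent correct at cut-off c is the average of p where q ≥ c and of 1 − p where q < c.

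**Mortality results**

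| Displayed risks | Mean displayed risk | Correct, cut-off 0.5 | Correct, cut-off 0.28 |
|---|---|---|---|
| Calibrated (d = 0) | 28% | 74.1% | 65.7% |
| Too low (d = −0.4) | 21.5% | 73.5% | 71.7% |
| Too high (d = +0.4) | 35.5% | 72.9% | 56.3% |

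At 0.5 the changes are 74.1 − 73.5 = 0.6 and 74.1 − 72.9 = 1.2 points (0.5 to 1.2 allowing for rounding). Calling every patient a survivor already scores 72.0%.

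**Too-extreme predictions, cut-off 0.5.** If the spread of the log-odds about its mean is multiplied by 1.5, the top tenth are told about 75% when about 60% die, and percent correct is 73.1%. If the log-odds themselves are multiplied by 1.5, percent correct is exactly unchanged, because nobody crosses 0.5.

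**Precision of percent correct.** √(0.72 × 0.28 / 500) = 0.020, and √(0.72 × 0.28 / 2500) = 0.009. The changes at 0.5 are within about one standard error in 500. In 2500 they are at most 1.2 / 0.9 = 1.3 standard errors. The calibrated value is also unknown in practice, so a reader who sees 72.9% has nothing to compare it with.

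**Precision of calibration in the same 500.** The standard error of calibration-in-the-large is 1/√(n × mean of p(1 − p)) = 1/√(500 × 0.177) = 0.106 logit. For a shift of 0.4, 0.4 / 0.106 = 3.8, which gives about 96% power at two-sided 0.05. The standard error of the calibration slope is about 0.12 to 0.14 for log-odds SDs of 1.05 and 0.87. The held-out sample can thus show what percent correct cannot.

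**All three outcomes, c-statistic 0.65 to 0.76, cut-off 0.5.** Halving the odds puts mean risk wrong by about 10 to 14 points and costs 0.3 to 2.8 points of percent correct. Multiplying the odds by 1.5 costs 1.0 to 2.7 points. Doubling them costs 3.4 to 8.2 points, so gross overprediction might be noticed.

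**The case against.** The strongest reply has five parts.

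1. **Percent correct is tied to internal validation only.** This stands. No measure is named for the 500, and it may sit in an analysis plan that is not shown. Its absence from a condensed article is no finding. The point rests on the measure that is named, which does not match the product.
2. **Goodness-of-fit statistics may include a calibration-type test.** This stands in part. Fit across the risk range is not right by construction, even in the fitting data. But the statistics are unspecified, come before validation, and do not reveal over-extreme predictions in new patients.
3. **Validation comes before the applications.** This stands. A reader might infer from the Discussion wording that release follows model creation and that validation is skipped. Statistical analysis describes validation first and then speaks of final models. What is unstated is only that the applications depend on the result.
4. **The errors used are large for this design.** This stands, so they are illustrations and not forecasts. The development intercept has a standard error of about 1/√(2500 × 0.177) = 0.048 logit, so 0.4 is about 8 standard errors. Over-extremeness by 1.5 (a slope near 0.67) would, by the heuristic shrinkage formula with a model chi-square of about 310 to 420, need about 310/3 = 103 to 420/3 = 140 parameters. With 30 parameters, shrinkage is 280/310 = 0.90 to 390/420 = 0.93. Because the 500 come from the same cohort, they also cannot show miscalibration in other populations.
5. **The insensitivity depends on the cut-off.** This is true. At 0.28 percent correct moves a good deal, but it improves when risks are too low, which makes it no better as a check on probabilities.

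**Conclusion.** The point holds in a limited form. The stated product is a probability, and the one named validation measure does not test probabilities. With 28% mortality and an assumed c-statistic of about 0.72, a 0.4 logit error in every risk changes percent correct by about 0.5 to 1.2 points at a cut-off of 0.5. At a cut-off equal to the event rate, the measure rewards risks that are too low by 6.0 points (71.7 − 65.7). Miscalibration could go undetected or be rewarded.

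A reader might infer that a miscalibrated bedside tool would be deployed. The article does not support that: nothing in it shows that the models will be miscalibrated, and the 500 may be assessed with suitable measures set out elsewhere. The sizes depend on the assumed c-statistic, the assumed cut-off and the size of the error supposed.

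**What to change.** - **Statistical analysis, validation paragraph.** Replace or supplement percent correct with calibration of the six-month probability as the application displays it. For each outcome, report calibration-in-the-large, calibration slope and a calibration curve, with confidence intervals, based on cumulative incidence for readmission. Correct these for optimism by resampling in the 2500 and report them in the held-out 500.
- **Statistical analysis and Discussion, application sentences.** State that the applications are built after this check.
- **Recalibration.** If it proves necessary, say that the recalibrated model no longer has an untouched validation sample. An automatic rule to recalibrate on the 500 would use up that sample and is not advised.

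The cost is a few more analyses on data already collected and a few sentences of text. The downside is that a calculator may be delayed.

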#### Geriatric conditions

General cognitive function is evaluated with the Telephone Interview of Cognitive Status (TICS) [17]. We chose the TICS because it can be administered in <10 minutes, can be used to detect mild as well as severe cognitive impairments, does not require writing (i.e. can be used despite visual or motor impairments), and can be converted to a Mini Mental State Examination (MMSE) equivalent [18]. In addition to general cognitive function, we include an assessment of executive function, which is relevant for specific tasks such as adherence to complex medical regimens after discharge, with the Controlled Word Association Test (COWAT) [19].

Vision questions are adapted from the Visual Functioning Questionnaire (VFQ-25); [20] participants are asked to rate their general vision on an ordinal scale (from “excellent” to “very poor”), and to indicate whether they have difficulty reading print or doing work or hobbies. Hearing is assessed with a global question (“do you have a hearing problem now?”) that has shown good sensitivity and specificity compared with audiography [21].

Muscle strength and functional mobility are important predictors of future disability and health status decline [22,23]. For muscle strength we chose to measure grip strength, which is assessed by the participant using their dominant hand to squeeze a handheld dynamometer (B&L Engineering, Santa Ana, CA); results are recorded in kilograms (kg) for three successive attempts. Functional mobility is measured with the Timed Get Up and Go (TUG) test [23], which requires the participant to rise from a seated position, walk 3 meters, and then return to the chair and sit down. The time it takes to complete this test in seconds is recorded, as well as a subjective rating of the person’s movements on a scale of 1–5 from normal to severely abnormal.

Activities of Daily Living (ADLs) [24] are measured with four interview items that assess whether participants are able to perform, without help from another person, the tasks of bathing, dressing, getting out of a chair, and ambulating. Participants are also asked how many falls they have had in the past year (from none to ≥ four).

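### The calculator takes only yes/no inputs, which fits poorly with the planned linearity checks and continuous measures: it either departs from the validated model or rests on dichotomised predictors

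*Protocol article*

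**What the plan says.** The Statistical analysis section of the protocol article describes the deliverable in two consecutive sentences. On what is stored: "The model coefficients for each outcome will be stored in hand-held applications whose outputs will provide the probability of each outcome". On what the user enters: "The inputs to the applications will consist of simple yes/no entries denoting the presence or absence of risk factors".

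The same section lists the predictors as "cardio-centric factors (e.g. STEMI vs. NSTEMI, systolic blood pressure, Killip Class), as well as geriatric impairments". Systolic blood pressure is measured on a continuous scale and Killip class is ordinal; only STEMI versus NSTEMI is binary by nature. The section also promises that "All linearity assumptions will be checked graphically".

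Under Geriatric conditions, the physical measures are collected as numbers. For grip strength, "results are recorded in kilograms (kg) for three successive attempts". For the Timed Get Up and Go, "The time it takes to complete this test in seconds is recorded".

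Two places lean towards binary coding. The models are to "predict the probability of each outcome for specific combinations of the risk factors", and Sample size and power speaks of explanatory variables with a prevalence of 30% to 50% and one relative risk each. No section states the scale on which any predictor enters a model.

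**The concern.** A yes/no predictor has no linearity assumption to check, so the linearity sentence anticipates predictors with more than two values. The input sentence allows none. Followed as written, the plan leads to one of two results.

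- **A continuous term stays in a final model.** Its coefficient is per unit (per mmHg, per kilogram, per second). A yes/no entry carries no value to multiply by it. The application must then use something other than the fitted model, and the performance found in the 500 validation participants does not describe it.
- **Every predictor is dichotomised before fitting.** The application then reproduces the model. The linearity check has nothing to act on in the final models, and a patient just past a cut-off gets the same contribution to risk as one far past it.

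The product is an individual probability. The Background states the hypothesis that adding geriatric conditions will give better discrimination than existing models, and it criticises those models for only modest discrimination in older patients. An avoidable loss of discrimination works directly against that aim.

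**Working it through.** **1. The plan's own figure.** The article states no C-statistic. The nearest figure is the 90% power in Sample size and power, which also shows how the predictors were pictured. With 2500 participants and 28% mortality there are 2500 × 0.28 = 700 events. For a binary factor of prevalence p and hazard ratio 1.3, at two-sided 0.05 (Schoenfeld):

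power = Φ(ln 1.3 × √(700 × p(1 − p)) − 1.96)

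- p = 0.3: Φ(0.2624 × √147 − 1.96) = Φ(1.22) = 88.9%
- p = 0.5: Φ(0.2624 × √175 − 1.96) = Φ(1.51) = 93.5%

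Readmission (975 events) gives 96.4% and 98.4%. The binding case agrees with the stated 90% to about one point. The figure is therefore sound, and it treats each predictor as present or absent.

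**2. Information kept when a normal predictor is split.** If the factor counts as present in a fraction p, with cut-point c = Φ⁻¹(1 − p) and normal density φ, the squared correlation between the yes/no version and the original is

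φ(c)² / (p(1 − p))

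- p = 0.5: 0.3989² / 0.25 = 0.64
- p = 0.4: 0.3863² / 0.24 = 0.62
- p = 0.3: 0.3477² / 0.21 = 0.58

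Over the article's own prevalence range, each continuous predictor loses 36% to 42% of its information.

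**3. Effect on the whole model.** This needs assumptions that the article does not supply: independent normal predictors; 4, 6 or 10 of them, with from about a fifth to all truly continuous and the rest binary; cuts at 30% or 50% prevalence; a yes/no odds ratio of 1.3 or 1.6 per factor; event rates of 28% or 39%. Logistic models were simulated with 400,000 subjects per scenario. The C-statistic with continuous terms kept was compared with that of the same predictors entered as yes/no.

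| Scenario | C, continuous kept | C, all yes/no | Loss |
|---|---|---|---|
| 4 predictors, 1 continuous, OR 1.3 | 0.572 | 0.564 | 0.008 |
| 10 predictors, 2 continuous, 50% cut, OR 1.3, 39% events | 0.620 | 0.612 | 0.008 |
| 6 predictors, 3 continuous, 30% cut, OR 1.6, 39% events | 0.663 | 0.635 | 0.028 |
| 6 predictors, 6 continuous, 30% cut, OR 1.6, 39% events | 0.681 | 0.633 | 0.049 |
| 10 predictors, 10 continuous, OR 1.6 | 0.724 | 0.667 | 0.057 |

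(Losses were computed before rounding.) Over all scenarios the loss is about 0.01 to 0.06, or roughly 6% to 27% of the excess of C over 0.5.

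**4. Effects nearer the article's own.** A relative risk of 1.3 at 28% mortality and 30% prevalence corresponds to risks of 0.334 and 0.257. That is an odds ratio of (0.334/0.666) / (0.257/0.743) = 1.45. With six predictors at odds ratio 1.45, the loss is 0.032 to 0.038 if all six are continuous and about 0.02 if three are. At odds ratio 1.3 the losses are 0.023 to 0.027 and about 0.015. A repeat simulation agreed with these values to within about 0.002.

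**The case against.** The strongest reply is that the article never says the models use continuous terms. Kilograms and seconds are recording scales, not modelling scales. Talk of impairments, of combinations of risk factors and of prevalence all suits present/absent coding, and a calculator fed with yes/no entries would reproduce such a model exactly. The linearity sentence may be generic, or may concern candidate variables before cut-points are chosen. Coding and cut-points are usually left to the analysis plan, which is not shown. Killip class can be entered as several yes/no indicators without loss. A quick bedside tool is also a legitimate aim.

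Much of this stands, and it rules out three readings that a reader might infer.

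- **That the application cannot reproduce the fitted model.** This follows only if a continuous term, or an ordinal factor kept as one graded term, stays in a final model. The documents do not settle that.
- **That the tool gives up much of its discrimination.** The loss is large for each continuous predictor but modest to moderate for the whole model. Six continuous predictors at log-odds 0.35 per SD take C from 0.71 to 0.67 or 0.66, but they imply yes/no odds ratios of about 1.7, stronger than the article plans for. They also leave no room for naturally binary factors such as STEMI versus NSTEMI.
- **That dichotomising costs as much as the geriatric variables add.** No figure in the article or in the calculations above supports this.

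The reply does not remove the point. The yes/no restriction is a stated rule, not an omitted detail. The dichotomised reading avoids the mismatch only by accepting the loss of information.

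**Conclusion.** The point holds in conditional form. The article fixes yes/no-only inputs applied to stored model coefficients, beside a continuous model factor and a linearity check. One reading gives an application that differs from the model validated in the 500 participants. The other gives an application that matches a model built on dichotomised predictors, each keeping about 58% to 64% of its information at the assumed prevalences.

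The likely cost of the second reading is about 0.01 to 0.06 in C, and about 0.015 to 0.04 with effects near the article's own and three to six of six predictors continuous. These sizes rest on independent, normal predictors with linear effects on the log-odds and on an assumed number of continuous terms; the documents give nothing to check them against. The cohort, the data collection and the power statement are unaffected. The deliverable is poorly specified and should be corrected before the models are built.

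**What to change.** Replace the yes/no sentence in the Statistical analysis section with: *Inputs are entered on the scale used in the model (numeric for continuous measures, levels for ordinal ones, yes/no for binary factors).* Add that continuous predictors stay continuous, with splines where the graphical check shows that linearity fails. The linearity sentence then has a purpose, and the application is the validated model.

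If a yes/no version is kept for bedside simplicity, make it a secondary score. Prespecify its cut-points, validate that exact version in the 500 participants, and report its C-statistic and calibration beside those of the full model so that users can see the price of the simplification.

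The cost is a few numeric fields in the application and slightly longer entry per patient. Blood pressure, grip strength and the timed walk are already collected as numbers, so no new data are needed.

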### Sample size and power

Of the SILVER-AMI cohort of 3000 participants, 2500 participants will serve as the development cohort and 500 will be randomly selected as the validation cohort. Based on 2008 Medicare data, we posited outcome rates of 39% and 28% for all-cause readmission and mortality. Based on previous research [29], we also assumed that a 10% decline in health status, as measured by the SF-36, would occur in 35% of surviving participants. With regard to the explanatory variables of primary interest, i.e., geriatric conditions and socio-demographic and clinical factors, we assumed each would exhibit measures of relative risk ≥1.3 for each time-to-event outcome and ≥1.5 for decline in health status. The 2500 participants in the development cohort provide 90% power to detect the stated magnitudes of relative risk for prevalence of the explanatory variables between 30% and 50%. For the validation sample, the accepted standard for time-to-event and logistic models should be large enough to contain a minimum of 100 outcome events [30]. For mortality, the least frequently expected outcome, the additional sample of 500 should allow for 140 events. The validation size of 500 will be preserved regardless of overall mortality and dropout.

